#### Surveillance report

2.6.2

The clinical research coordinator will collect the date of surveillance, type of surveillance performed (ie*,* urine testing or cystoscopy, or standard or enhanced cystoscopy), results of surveillance testing (negative, suspicious, or positive), and next step recommended by the provider. This will allow us to ascertain the type of surveillance that each participant underwent, which will serve as a fidelity measure.

We will also record any evaluations or treatments received since the last visit. This will include dates and results of any for-cause evaluations (eg, cystoscopy or upper tract imaging done for hematuria), and dates and pathology of any bladder biopsies or resections, of any intravesical treatments, and of other bladder cancer–directed therapy. These data will allow us to calculate the number of invasive procedures that each patient underwent during the study period (exploratory outcome).

#### Surveillance discomfort (exploratory outcome)

2.6.3

The participant will be asked immediately after the cystoscopy or after providing a urine sample (depending on the arm and visit) to rate their discomfort on a visual analog scale ranging from 0 (no pain) to 10 (worst pain).

#### Bladder cancer recurrence/progression

2.6.4

Bladder cancer recurrence is defined as any bladder abnormality detected during study follow-up, which is biopsied or resected, with local pathology confirming urothelial carcinoma. Note that we require pathological confirmation of recurrence; thus, in-office fulguration without biopsy should not be performed.

Bladder cancer progression is defined as stage or grade progression according to the International Bladder Cancer Group [23], development of metastatic disease, or bladder cancer death. The clinical research coordinator will perform a chart review after each surveillance visit and at participant termination. For participants who developed a recurrence or progression, pathological details of this recurrence or progression will be abstracted from the chart. Following data collection, these participants will be withdrawn from the study and will undergo further treatment and surveillance as per the standard of care.

### Study setting and recruitment

2.7

Consecutive patients, 18 yr and older, undergoing surveillance for low-grade intermediate-risk bladder cancer will be approached for participation if their first surveillance cystoscopy ≤4 mo after tumor resection shows no evidence for recurrence. We anticipate that the population for this study will include individuals with diverse demographic characteristics from three locations throughout the USA (Charleston, SC; Dallas, TX; and White River Junction, VT). The protocol allows for opening the study at additional sides as needed.

Each site’s principal investigator will present the study protocol to the appropriate local clinical care providers so that those involved in the care of potential participants are familiar with the protocol requirements. Each site will have at least one dedicated clinical research coordinator to facilitate enrollment.

Each site’s principal investigator and clinical research coordinator will work with the clinical care team to identify patients scheduled for surveillance cystoscopy ≤4 mo after tumor resection, who meet the study inclusion criteria. The screening and recruitment procedures will include tracking of all screened and approached patients according to the Screening, Eligibility, Approach, Randomization (SEAR) framework [24].

Electronic health data will be used to identify potentially eligible patients. Specifically, study teams will regularly review lists of patients scheduled for cystoscopy procedures and lists of patients who underwent recent bladder biopsy or transurethral resection. These patients will then be prescreened for potential eligibility by clinical research coordinators using the electronic health record, with data recorded as part of the SEAR framework described above. After preliminary consultation and eligibility assessment by a potential participant’s clinical team, the participating site’s clinical research coordinator will approach each patient immediately after their surveillance cystoscopy to discuss enrollment and informed consent (see the Supplementary material for model informed consent form). We anticipate recruitment of 240 participants over approximately 3 yr.

### Randomization

2.8

A participant will be enrolled in the study once screened for eligibility and after providing written informed consent. After enrollment, the clinical research coordinator will enter the patient study ID number and stratification factors (site, sex, and receipt of prior intravesical therapy) into the secure online Research Electronic Data Capture (REDCap) system [25] to obtain a study arm assignment. The assignment will be based on the randomization lists provided by the statistician. The list of randomization with 1:1:1 allocation is stratified by site, sex, and receipt of prior intravesical therapy, and was created with permuted blocks of size 6. Receipt of intravesical chemotherapy is defined as treatment with bacillus Calmette-Guérin (BCG) or with intravesical chemotherapy in the 12 mo prior to enrollment.

The clinical research coordinator will then convey the assignment to the treating clinician and participant, and assist with scheduling surveillance visits according to study arm assignment. Given the pragmatic nature of this healthcare delivery study, the participants, clinical staff, and clinical research coordinators cannot be blinded to intervention assignment. However, we will assure that interventions are coded in a way that analytical staff will be blinded to interventions until the analysis phase for the primary outcome is completed.

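### One fixed, published block size of 6 in an open-label trial lets an attentive site coordinator work out some upcoming assignments; varying, undisclosed sizes would largely prevent this

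*Protocol article*

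**What the plan says.** Section 2.8 (Randomization) fixes the scheme: "The list of randomization with 1:1:1 allocation is stratified by site, sex, and receipt of prior intravesical therapy", and it "was created with permuted blocks of size 6". No second size and no random variation is mentioned. The statistician prepares the list, and REDCap releases the arm once consent is given and the stratification factors are entered.

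The same section says that "the participants, clinical staff, and clinical research coordinators cannot be blinded to intervention assignment". Blinding is promised only for analytical staff. "The clinical research coordinator will then convey the assignment to the treating clinician and participant".

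Section 2.7 (Study setting and recruitment) gives the same role the enrolment work. Coordinators prescreen from the electronic health record, and the "clinical research coordinator will approach each patient immediately after their surveillance cystoscopy to discuss enrollment and informed consent". Patients are to be approached consecutively, and everyone screened or approached is logged under the SEAR framework. The trial starts at "three locations throughout the USA", with more sites allowed, and plans for 240 participants.

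**The concern.** Concealment needs more than a hidden list. Whoever recruits must also be unable to infer the next entry. Here one role sees each past assignment, can probably read sex and earlier intravesical treatment from the record before the approach, and can look up the block size. Because site is a stratification factor, each sequence belongs to one site, whose staff see all of it. Release through REDCap hides the list but not its history.

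A coordinator who knows that the next slot is cystoscopy, or is not, could change who is approached or how the trial is presented. The primary outcome is a patient's own rating of urinary quality of life, so a difference in who enters which arm could carry into the comparison.

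**Working it through.** The article states no predictability figure, so there is none to reproduce.

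**Inputs.** From section 2.8: block size 6 and 1:1:1 allocation, hence 2 slots per arm per block. From sections 2.7 and 2.8: 3 sites × 2 sexes × 2 prior-therapy levels = 12 strata, 4 per site. From section 2.7: 240 participants. That averages 240/12 = 20 per stratum, or 20/6 = 3.3 blocks.

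**Complete blocks.** There are 6!/(2!·2!·2!) = 90 equally likely orderings.

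- *Next arm fully determined.* Position 6 always is. Position 5 is when the last two slots belong to the same arm: 3 of 15 pairs = 1/5. Average: (1 + 1/5)/6 = 20%, or at most 48 of 240.
- *Certain whether cystoscopy or urine test.* Both cystoscopy slots are already used, or only cystoscopy slots remain. Position 3: 1/15. Position 4: 3/15. Position 5: 6/15 + 1/15 = 7/15. Position 6: 1. Average: (1/15 + 3/15 + 7/15 + 1)/6 = 28.9%.
- *At least one arm excluded.* Positions 3 to 6: 0.2, 0.6, 1, 1. Average over six positions: 2.8/6 = 46.7%.
- *Best guess correct.* Positions 1 to 6: 0.333, 0.4, 0.5, 0.533, 0.6, 1. Average: 56%, against 33% by chance.

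**Incomplete last blocks.** Enrolment ends partway through a block in most strata, so late positions are under-represented. I simulated 240 patients over the 12 strata. The shares are assumptions, because the article gives none: sites equal or 50/30/20, women 10–50%, prior therapy 30–50%.

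| Setting | Fully determined | Cystoscopy versus urine test certain |
|---|---|---|
| Complete blocks | 20% | 28.9% |
| 3 sites, 12 strata | about 17–18% (42–43 of 240) | about 26% (about 62 of 240) |
| 6 equal sites (20% women, 30% prior therapy) | about 15% (about 37 of 240) | about 23% (0.234 × 240 = about 56) |

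The three-site figures barely move across the assumed shares.

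**Varying sizes.** With 20 patients per stratum, and a guesser who knows the set of sizes but not their order:

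| Block sizes | Fully determined | Cystoscopy versus urine test certain | Best guess correct |
|---|---|---|---|
| 6 only | 17.9% (about 43) | 25.8% | 54% |
| 3/6/9 | 2.9% (about 7) | 5.2% | 53% |
| 6/9/12 | 1.9% (about 5) | 3.5% | 51% |

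Varying sizes remove most of the certainty. They improve the average guess only a little.

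**The case against.** The strongest reply is that the protocol already guards against the harm in question. Approach is consecutive and tied to a fixed event, the clinical team assesses eligibility first, the arm is released only after written consent, and SEAR logs everyone screened or approached. Skipping a patient would leave a trace. In section 3.2.2 the 3-month score is part of the longitudinal outcome and the test uses arm-by-time interactions, so a stable difference in baseline score is absorbed. A complementary analysis adjusts for that score directly.

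Much of this stands. But these measures deter and help detect selective approach; they do not make the next slot less predictable, and a log of approaches does not show how the trial was described. The baseline score is also an imperfect shield, because section 2.6.1 schedules that survey one to seven days after consent/randomization, when the participant may already know the arm.

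It also stands that the percentages assume perfect tracking. Section 2.7 provides at least one coordinator per site, so where there are several they would have to pool what they know.

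A reader might infer that patients' liking for urine tests gives any steering an obvious direction. The article does not support that. Section 1.3 makes the preference conditional on the test being proven safe, and sections 1.5 and 2.2 record worry among patients and urologists about missed cancer.

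**Conclusion.** The point holds as a modest, avoidable weakness in allocation concealment. With the stated scheme, up to about 17–18% of assignments (42–43 of 240) can be known in advance, and for about 26% (about 62 of 240) it can be known whether cystoscopy or a urine test comes next. Both figures are upper bounds. They rest on three sites, the assumed stratum shares and a coordinator who follows all four strata at the site; they fall with more sites.

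Two stronger readings go too far. One is that the complete-block rates apply to the whole trial (28.9% of 240 is about 69); that ignores unfinished blocks. The other is that the scheme produces baseline differences which no analysis can repair. The article shows opportunity only. Nothing in it indicates that selection has occurred, and the baseline handling would absorb stable differences in the score. What remains is that selection or differences in presentation could still bias a subjective outcome. This is a cheap improvement, not an error that undermines the design.

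**What to change.** For assignments not yet made and for any added site, have the statistician generate new lists with randomly varying block sizes in multiples of 3, for example 3/6/9 or 6/9/12. Withhold the sizes and their order from site staff and keep them out of public documents until enrolment ends; until then the protocol need say only that block sizes vary at random. The article describes recruitment in the future tense, which suggests, but does not prove, that assignments remained to be made when it appeared.

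The cost is regenerating the unused lists, reloading them in REDCap and accepting slightly more possible imbalance in small strata. The largest within-block difference between two arms equals the slots per arm: 6/3 = 2 now, up to 9/3 = 3 or 12/3 = 4 with the larger sets. Sample size, outcome and analysis are unchanged.

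For assignments already made, use the SEAR log to compare approach and consent rates by the block position of the next open slot in the patient's stratum, and report the result. This can reveal selective approach or consent, but it cannot show how the trial was presented.

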### Data management

2.9

Data will be entered into electronic case report forms. The data system includes password protection and internal quality checks, such as automatic range checks, to identify data that appear inconsistent, incomplete, or inaccurate. Clinical data will be entered directly from the source documents. Clinical monitoring will be overseen by an internal oversight committee (IOC). The IOC will include the lead principal investigator, site principal investigator for each of the included sites, study statistician, and central project manager. The IOC will meet via monthly video conference and will review reports for each site to compare whether surveillance was administered according to randomized allocation.

The central project manager will conduct random monitoring of target data, including, but not limited to, verification of signed consent documents, inclusion criteria, phone survey data, type of surveillance, and results of surveillance. The IOC will oversee central monitoring. This will include assessing the following for each site: data entry errors, missing data, and responsiveness to data queries from the central study team. In addition, the IOC will assign the cause of death for any patients who die during study follow-up. Site investigators and clinical research coordinators will be contacted as needed for retraining and technical assistance if systematic data integrity issues are discovered at their site. The IOC will review and approve a monthly data integrity report, which will be stored for record keeping.

## Statistics

3

We assumed 20% missing data for the primary outcome at each time point. In line with prior work [28], we assume that cancer recurs at a rate of 10%/yr (exponential distribution). Patients see bladder cancer surveillance visits as the highest priority [29]—as such attrition is expected to be low. However, we have conservatively assumed a 10% attrition rate per year.

The simulation is based on the power to show that at least one of the urine test arms is superior to the frequent cystoscopy arm at a Bonferroni corrected 0.025 type 1 error rate, within a mixed-effect model with a random effect for the participant and a structural model with a main effect for the 6-, 12-, 18-, and 24-mo time points and their interaction with the study arm. This is similar to the power of a multivariate Wald test of the equivalence of all three arms at a type 1 error rate of 5%.

Under these assumptions, our study of 240 participants (80 participants per arm) has sufficient power (80%) to detect an effect size of 0.6 standard deviations (green cell in Table 3). This corresponds to a concordance (Mann-Whitney proportion) of 66%. That is, we assume that 66% of the time, a participant who was randomized to a urine testing arm will have a significantly better urinary domain score at 6 or 18 mo than a person who was randomized to the frequent cystoscopy arm.

We acknowledge that the trial is not adequately powered to address some of the exploratory outcomes, for example, complications, bladder cancer recurrence, and bladder cancer progression, given the rarity of these outcomes. Analyses will account for sex as a biological variable using it as a potential covariate in statistical models and subgroup analyses. Given that this is a phase 2 healthcare delivery trial, we will have limited power to determine whether sex modifies the treatment effect. However, if women had zero change in urinary quality of life with urine testing while men would have an improvement of 1.4 standard deviations on the urinary symptom domain scale, we would have 80% power to detect the heterogeneity of treatment effect.

### Analyses plans

3.2

#### Populations for analyses

3.2.1

The intent-to-treat population is defined as the population of participants who were randomized to any of the study arms. The participants will be categorized (in terms of their intervention assignment) based on their initial randomized group and will be included in analyses irrespective of their status—completer or dropout before completion.

The safety population includes all the participants who were consented to the trial, randomized to any of the arms, and completed at least one postrandomization surveillance visit.

#### Primary outcome analyses: urinary quality of life

3.2.2

The primary outcome is the patient-reported urinary quality of life domain score of the validated QLQ-NMIBC24 instrument [20], measured as a repeated measure at each surveillance visit. We will model the primary outcome urinary quality of life in terms of the study arm and time using a mixed-effect model with a random intercept for the participant. We will include fixed effects for the study arm (indicators for the Xpert Bladder Cancer Monitor and the EpiCheck urine test with the frequent cystoscopy arm as the referent, ie*,* intent–to-treat analyses), for time points (3, 6, 12, 18, and 24 mo) as categorical variables (3-mo baseline as referent), and the interactions of the study arm and time point. The interaction provides information about the treatment efficacy and is analogous to a difference in difference. We will also add a fixed effect for sex as a biological variable, given that women’s urethras are much shorter than men’s, which may very well affect urinary quality of life after surveillance testing. Results from these models will be presented as adjusted means with standard deviations.

As a complementary analysis, we will employ a generalized estimating equation (GEE) with the same fixed effects and cluster with respect to the participant using an autoregressive 1 correlation structure. As another evaluation of the robustness of findings, we will repeat the mixed effects and GEE analysis above, removing the 3-mo baseline value from the longitudinal vector of urinary quality of life and instead add it as a covariate (fixed effect) and eliminate the interaction from the model; the information on efficacy from these complementary analyses is in the main effects for the study arm. If these complementary analyses do not confirm the findings from the primary analyses, we will explore the reasons for the divergent results and report these with our main study findings.

The hypothesis tests of primary interest are whether urinary quality of life scores are improved 1–3 d after surveillance with urine testing relative to surveillance with frequent cystoscopy. For participants with a positive or nondiagnostic urine test, this outcome will be ascertained 1–3 d after the cystoscopy triggered by the urine test. Each of the two urine test modalities will be compared with the frequent cystoscopy arm, using the Bonferroni-Holm method [30] to control the family-wise type 1 error rate at 5%. Each of these two tests (each urine test vs frequent cystoscopy arm) will be conducted using a multivariate Wald test that averages the corresponding coefficients from the 6- and 18-mo time points from the interaction of the study arm with time points. If there is a significant effect of urine test modalities (done at 6 and 18 mo) compared with the frequent cystoscopy arm, we will test whether the effect is different at 6 versus 18 mo.

All analyses will be performed using intent-to-treat principles and within the intent-to-treat population. For example, if a patient in a urine test arm does not complete a urine test and has a cystoscopy instead at 6 or 18 mo, we will nonetheless analyze this patient’s outcome data from this time point as in a urine test arm.

We do not anticipate that missing data will be a major issue as each site will have at least one staff member dedicated to obtaining the primary outcome data, that is, validated urinary quality of life domain scores, 1–3 d after the surveillance visit. Based on a similar prior longitudinal study validating the QLQ-NMIBC24 [20], we assume 20% missing data for the primary outcome at each time point.

Missing outcomes can be analyzed as is using the mixed-effect model for longitudinal data described above, under the assumption that the distribution of the outcome in participants for whom it is not missing does not differ from the distribution in those in whom it is missing conditional on previous observations of the outcome and covariates. We will also carry out sensitivity analyses to determine to what extent conclusions are sensitive to departures from this missing at random assumption. Our longitudinal analytic approach described above allows us to incorporate study data even if study visits were missed or participants were lost to follow-up.

#### Subgroup analyses

3.2.3

We will add a fixed effect for sex as a biological variable into our analytic models, given that women’s urethras are much shorter than men’s, which may very well affect urinary quality of life after surveillance testing. Results from these models will be presented as adjusted means with standard deviations, stratified by sex.

Similarly, we will add a fixed effect for race into our analytic models and present results as adjusted means with standard deviations, stratified by race.

Additional subgroup analyses may be added to the statistical analysis plan. These may also be performed post hoc if approved by the IOC.

Given that this is a phase 2 healthcare delivery trial, we will have limited power to determine whether sex modifies the treatment effect. Similarly, power will be limited for any other subgroup analyses.

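### The sex and race subgroup models add only a main effect, so they force the same treatment effect in every subgroup and cannot address the effect modification by sex that the protocol asks about

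*Protocol article*

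**What the plan says.** Section 3.2.2 models the urinary score with arm, categorical time, arm-by-time interactions and a random participant intercept. It locates the treatment effect in the arm-by-time terms: "The interaction provides information about the treatment efficacy and is analogous to a difference in difference". The primary contrast averages the 6- and 18-month terms. The same section adds sex to this model: "We will also add a fixed effect for sex as a biological variable".

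Section 3.2.3 then describes the subgroup analyses. For sex: "We will add a fixed effect for sex as a biological variable into our analytic models", followed by "Results from these models will be presented as adjusted means with standard deviations, stratified by sex". For race: "we will add a fixed effect for race into our analytic models and present results as adjusted means with standard deviations, stratified by race". On the purpose of the sex analysis it states that "we will have limited power to determine whether sex modifies the treatment effect".

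Section 3.1 gives a scenario of no improvement in women and 1.4 SD in men, and says that in this case "we would have 80% power to detect the heterogeneity of treatment effect".

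The article states no interaction of sex or race with arm, or with arm and time.

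**The concern.** A subgroup analysis of effect modification needs a parameter that lets the arm effect differ between subgroups. The models in section 3.2.3 have none. For sex, the subgroup model is the primary model over again.

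If the plan is followed as written, the tables by sex and by race will show equal arm effects in every subgroup, and that equality comes from the model. A reader could take it as evidence that the benefit of urine testing is the same in men and women. The protocol gives an anatomical reason to expect that sex may matter here, so the misreading would have consequences.

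**Working it through.** **1. Algebra of the stated model.** Let s = 1 for women and 0 for men, arm 0 be frequent cystoscopy, and t = 3 the baseline. The mean is

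μ(a,t,s) = α + β_a + γ_t + δ_at + θ·s, with δ_a,3 = 0.

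The treatment effect of arm a at visit t in sex s is

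[μ(a,t,s) − μ(0,t,s)] − [μ(a,3,s) − μ(0,3,s)] = (β_a + δ_at) − β_a = δ_at.

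The term θ·s cancels within each bracket. The averaged contrast, (δ_a,6 + δ_a,18)/2, does not depend on s, so men and women have the same effect for any data set. Replacing θ·s with one constant per race group gives the same result. The constant still shifts mean scores, so a difference in level between the sexes would be visible.

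**2. Numerical illustration.** From section 3.1: 0 SD in women, 1.4 SD in men, 240 participants in three equal arms, five time points, exchangeable correlation 0.7. Assumed: 25% women (the article gives no share), no missing data, no dilution by positive urine tests. Twenty simulated trials, mean 6/18-month effect:

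| Model | Men | Women |
|---|---|---|
| arm × time + sex (as stated) | 1.05 SD | 1.05 SD |
| arm × time × sex | 1.37 SD | 0.00 SD |

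Under the stated model the largest difference between the sexes in any trial was 2 × 10⁻¹⁶, which is rounding error. The common value is the sex-weighted average, 0.75 × 1.4 + 0.25 × 0 = 1.05. With 5% women it would be 0.95 × 1.4 = 1.33. The size depends on the assumed share; the equality does not.

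**3. What the quoted 80% refers to.** The article's 66% concordance reproduces: Φ(0.6/√2) = 66.4%. The 80% at 1.4 SD cannot be reproduced from the article alone, because the share of women is not given. I computed power for a sex-by-arm contrast averaged over 6 and 18 months, using the stated sample size, correlation, 20% missing data per visit, and 10% per year each for recurrence and attrition. I assumed two-sided tests at 0.025, with success if at least one arm is significant, and recurrence at 5% of visits. The effect is diluted by the share of visits without a triggered cystoscopy:

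- Xpert: 0.95 × 0.76 + 0.05 × 0.28 = 0.736
- EpiCheck: 0.95 × 0.84 + 0.05 × 0.26 = 0.811

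At 10% women the standard errors are 0.417 and 0.426. The standardised effects are 1.4 × 0.736/0.417 = 2.47 and 1.4 × 0.811/0.426 = 2.67, against a critical value of 2.24. Allowing for the shared control arm, the power for at least one arm is 79%. Over the range:

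| Women | 5% | 8% | 10% | 12% | 15% | 20% | 25% |
|---|---|---|---|---|---|---|---|
| Power at 1.4 SD | 53% | 67% | 79% | 84% | 90% | 96% | 98% |

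These powers exist only for a model with an interaction. The same method gives about 98% power at the main 0.6 SD effect (80% at about 0.43 SD), so it does not reproduce the article's main figure either. The body of Table 3 and the simulation code are not available, so I do not call either figure wrong, and I do not infer which share of women was assumed.

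**The case against.** The best defence is that the wording is loose. Section 3.2.3 adds presentation by subgroup to what section 3.2.2 already promises, which would be pointless if only a constant shift were meant, and it speaks of effect modification. Separate fits or an interaction may have been intended. But the text takes the subgroup means from the models that contain the fixed effect. Within one sex that effect cannot be estimated, and separate fits alone give no test of heterogeneity. Where the authors want an interaction, as for arm and time, they name it.

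A second defence is that the article is condensed and the analysis plan may supply the terms. Section 3.2.3 leaves only additional subgroup analyses to that plan. For sex and race it states a model, and the point concerns that stated model.

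A third is that limited power is admitted. That stands and lowers the stakes, but low power means an imprecise estimate, whereas this model fixes the difference at zero.

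A reader might also infer more than the article supports:

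- That heterogeneity by sex is a trial aim. It is a subgroup question; the objective in section 2.3 compares arms.
- That no sex difference of any kind would be reported. A difference in mean level would be.
- That a heterogeneity claim with quoted power is also made for race. Power is quoted for sex only.
- That the 1.4 SD figure is wrong, or that it reveals a particular share of women. Without that share and the simulation, neither follows.

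**Conclusion.** The concern holds as a mismatch between the stated model and the stated question. As written, the arm effects at 6 and 18 months are equal across sex and across race groups by construction. That conclusion is algebraic and needs no assumption beyond reading the fixed effect as a main effect, which is what the text supports. The 80% power for heterogeneity by sex belongs to a test that the article does not describe. The 1.05 SD illustration and the power table rest on assumed shares of women and only indicate scale. The primary contrast, its error control and the sample size are untouched, so this is a worthwhile correction to a secondary analysis.

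**What to change.** For sex, add sex-by-arm-by-time terms with all lower-order terms. Test the sex-by-arm contrast averaged over 6 and 18 months, and report the arm differences for men and for women with 95% confidence intervals, labelled exploratory. State beside the 80% figure the share of women it assumes.

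For race, use the analogous interaction, collapse categories where cells are sparse, and make no power claim.

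The cost is a change of wording and a little more analysis. Sex is already a stratification factor, and race is already planned as a model term. The downside is wide intervals in small subgroups, which describe the available information honestly.
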